## Abstract

**Background:**

The prevalence of type 2 diabetes mellitus (T2DM) is increasing worldwide. T2DM is associated with serious macro- and microvascular complications. In particular, diabetic kidney disease (DKD), which begins with excessive urinary albumin excretion, has a significant impact on affected individuals and is costly to healthcare services. Inhibition of the renin–angiotensin–aldosterone system (RAAS) with angiotensin converting enzyme inhibitors (ACEI) or angiotensin receptor blockers (ARB) significantly reduces albuminuria in diabetes, but this effect is not observed in all those treated. Active vitamin D analogues have been observed to be reno-protective through inhibition of RAAS in animal and human studies. Therefore, it can be hypothesised that an active vitamin D analogue will have an additional benefit to ACEI/ARB treatment for albuminuria reduction in DKD.

**Methods:**

The planned study is an ongoing non-blinded randomised controlled parallel-group trial examining the impact, in individuals with T2DM, of the addition of bioactive vitamin D (calcitriol) to RAAS inhibition treatment using ACI or ARB on urinary albumin excretion over a period of 26 weeks. The primary outcome measure is the urinary albumin creatinine ratio. It is planned for the study to recruit 320 participants. Other outcome measures of interest include 24-h urine albumin (24 h UA) excretion, estimated glomerular filtration rate (eGFR), blood pressure and quality of life. Safety will be assessed throughout.

**Discussion:**

If the addition of calcitriol to RAAS inhibition with ACEI or ARB safely results in a significant reduction in albuminuria, the study adds to the body of evidence supporting a role for vitamin D in reno-protection, will inform clinical practice and could result in significant reduction of healthcare costs associated with DKD.

**Trial registration:**

ISRCTN, ISRCTN86739609. Registered on 7 June 2017. ClinicalTrials.gov, NCT03216564. Registered on 13 July 2017.

**Electronic supplementary material:**

The online version of this article (10.1186/s13063-018-2616-5) contains supplementary material, which is available to authorized users.

## Background

The prevalence of type 2 diabetes mellitus (T2DM) has reached pandemic proportions. T2DM is syndemic with obesity, whose prevalence has also increased dramatically worldwide. T2DM is associated with macrovascular (ischaemic heart disease, stroke and peripheral vascular disease) and microvascular (nephropathy, retinopathy and neuropathy) complications. Of those with diabetes, 30–50% will develop kidney disease and are at risk of progressing to end-stage renal disease (ESRD) [1]. Diabetic kidney disease (DKD) is the leading cause of ESRD worldwide [1, 2]. Once ESRD occurs, there is a significant individual burden of increased cardiovascular risk and reduced quality of life as well as requirement for renal replacement therapy and transplantation with increased healthcare costs.

Renin–angiotensin–aldosterone system (RAAS) blockade with an angiotensin converting enzyme (ACE) inhibitor (ACEI) or angiotensin II type I receptor blocker (ARB) is the most widely used strategy to slow the progression of DKD in both type 1 diabetes mellitus [3] or T2DM [4, 5]. RAAS blockade reduces blood pressure, the mean rate of decline in glomerular filtration rate (GFR) by 2–10 mL/min per year and albuminuria in DKD [4, 5]. However, not all those treated achieve adequate control of blood pressure, a reduction in albuminuria or prevention of a decline of renal function [6].

Several mechanisms, including polymorphisms in the ACE gene, have been proposed to account for the variability of response to RAAS therapy [7]. An emerging hypothesis is that RAAS blockade leads to compensatory stimulation of the RAAS, contributing to therapy resistance [8]. Thus, therapeutic approaches directed at suppression of the compensatory increase in the RAAS are increasingly sought [9].

Experimental and clinical evidence suggest that vitamin D may be reno-protective in chronic kidney disease (CKD), including DKD [10–15]. In animal models of glomerular injury, 1,25-dihydroxycholecalciferol (1,25-(OH)_2_-D3; calcitriol) ameliorates glomerular injury [16] and enhances renal protection by suppressing transforming growth factor β (TGF-β)-induced α-smooth muscle actin production and type 1 collagen [17], and by increasing hepatocyte growth factor [17]. Vitamin D analogues have been reported to decrease glomerular podocyte loss and podocyte hypertrophy [18]. 1,25-(OH)_2_-D3 is a negative regulator of the RAAS. Vitamin D deficiency stimulates renin expression in normal mice and injection of 1,25-(OH)_2_-D3 reduces renin synthesis [18]. Rats with the remnant kidney model of CKD treated with the vitamin D_2_ analogue paricalcitol (19-nor-1,25-dihydroxyvitamin D_2_) showed reductions of 30–50% in kidney tissue messenger RNA (mRNA) and protein levels of angiotensinogen, renin, renin receptor and vascular endothelial cell factor, and amelioration of glomerular damage and proteinuria compared to untreated rats [19]. Diabetic mice lacking the vitamin D receptor develop more severe nephropathy than wild-type mice suggesting that vitamin D is reno-protective by suppressing the RAAS [19]. Zhang et al. demonstrated that combination therapy with the AT1 receptor blocker losartan and paricalcitol prevented albuminuria, restored glomerular filtration barrier structure and reduced glomerulosclerosis in diabetic mice, and that these changes were associated with suppression of intra-renal renin and angiotensin II, as well as transforming growth factor- β (TGF-β) [19, 20]. This group reported similar and long-term suppression of the RAAS and reduction of proteinuria using another vitamin D_2_ analogue, doxercalciferol, in experimental diabetic nephropathy [21]. In humans, observational data suggest an inverse relationship between serum 25-hydroxyvitamin D levels and both albuminuria [22] and progression of CKD [23]. Small, clinical studies show that vitamin D therapy may be useful in reducing glomerular injury in IgA nephropathy and CKD [24–26]; a secondary analysis of clinical trials of paricalcitol therapy suggested that this agent is associated with a reduction of proteinuria in individuals with various forms of CKD [27]. In a randomised clinical trial (VITAL study), de Zeeuw et al. reported that the addition of paricalcitol to RAAS inhibition safely reduces albuminuria in those with T2DM [28].

### Study rationale

The striking histologic, molecular and hormonal improvements observed with vitamin D in experimental kidney disease, coupled with promising preliminary clinical results observed in humans, provides the rationale for the IDEAL-2 (Intervention using vitamin D for elevated urinary albumin in type 2 diabetes mellitus) study. IDEAL-2 is a non-blinded randomised controlled trial (RCT) aiming to examine the impact of the addition of the active form of vitamin D (1,25-(OH)_2_-D3; calcitriol) to ACEI or ARB in T2DM individuals with albuminuria. Calcitriol was chosen as the active form of vitamin D because of its availability in Qatar.

### Hypothesis

Our primary hypothesis is that bioactive vitamin D (1,25-(OH)_2_-D3 [calcitriol]), added to inhibition of the RAAS, via ACE inhibition or ARB, has a differential impact on urine albumin excretion in T2DM compared to RAAS inhibition alone.

### Primary objective

The primary objective of IDEAL-2 is to examine the effect of calcitriol + ACEI or ARB therapy on urine albumin to creatinine ratio (ACR; measured in a standard clinical biochemistry laboratory) compared to ACEI or ARB therapy alone, after 26 weeks, in individuals with type 2 diabetes (T2DM).

### Secondary objectives

The secondary objectives of IDEAL-2 are to compare calcitriol + ACEI or ARB therapy to treatment with ACEI or ARB alone after 26 weeks for:24-h urine albumin (24 h UA) excretion;Estimated glomerular filtration rate (eGFR);Blood pressure;Quality of life (measured using the EQ-5D questionnaire).

### Tertiary objectives

#### Diabetes complications

The study will examine the impact of the interventions on other diabetes complications. Neuropathy will be assessed using the Michigan Neuropathy Screening Instrument (MNSI) [29, 30] and physical examination. Retinopathy will be assessed through retinal photography. The Vicorder device will be used to assess measures of arterial stiffness [31].

#### Biomarkers

The study will examine circulating and urinary biomarkers associated with disease severity, disease progression and treatment response. A key objective is to develop urinary mRNA/microRNA (miRNA) biomarkers predictive of response to therapeutic interventions. Our assessment of urinary mRNA and miRNA may also provide mechanistic insights into the disease process as well as suggest mechanisms for the therapeutic outcomes. We will perform mRNA and miRNA profiling of urine collected before randomisation (baseline) and at 26 weeks of treatment and investigate whether urinary cell mRNA/miRNA profiles are associated with baseline albuminuria and eGFR in the individuals enrolled in the study and whether the urinary cell mRNA/miRNA profiles are associated with changes in albuminuria and eGFR following intervention. Our urinary mRNA profiling strategy has been successfully adapted by others to predict disease activity and progression of native kidney disease including diabetic nephropathy [32, 33]. We will utilise this assay for the measurement of urinary cell levels of mRNAs for proteins implicated in diabetic nephropathy (e.g. TGF-β1), mRNAs that may be regulated by vitamin D (e.g. renin) and podocyte-associated mRNAs (e.g. podocin). We have previously demonstrated the clinical utility of urinary cell profiles in renal allograft recipients [34–39].

Podocyte-specific loss of functional miRNAs in mice results in proteinuria, glomerular and tubular injury, renal failure and death [40–42]. miR-192 and miR-377, both upregulated by TGF-β1 in mesangial cells, are hyper-expressed in mouse models of diabetic nephropathy [41, 42]. Recently, TGF-β1 and β2 were shown to downregulate miR-200a, a miRNA with potential for preventing renal fibrogenesis [43]. Also, a loss of miR-192 has been associated with fibrogenesis in humans [44]. Wang et al. recently reported that urinary levels of miR-200a-200b and -429 are low in individuals with IgA nephropathy compared to healthy controls, and that ‘the degree of reduction correlated with disease activity and rate of progression’. Moreover, an inverse association of urinary expression of ZEB2 mRNA with miR-200b and that of vimentin mRNA with miR-200a was observed [45].

## Methods

IDEAL-2 is an ongoing non-blinded randomised controlled parallel-group trial examining the impact of the addition of bioactive vitamin D (calcitriol) to RAAS inhibition treatment using ACEI or ARB on urinary albumin excretion. The reported protocol follows the SPIRIT (Standard Protocol Items: Recommendations for Interventional Trials) recommendations (http://www.spirit-statement.org/; see Additional file 1: SPIRIT checklist). 

Ethical approval for the study has been obtained from the Hamad Medical Corporation IRB, Weill Cornell Medicine – Qatar IRB and the Ministry of Public Health, Doha, Qatar. The study is supported by the Weill Cornell Medicine – Qatar Institutional Data and Safety Monitoring Board (DSMB) consisting of statisticians and physicians. Study audit will be conducted at three-monthly intervals by the Clinical Research Core, Weill Cornell Medicine – Qatar following a standardised protocol. The trial is registered at ISRCTN (ISRCTN86739609, date assigned 7 June 2017) and ClinicalTrials.gov (NCT03216564, registered on 13 July 2017). The description of the protocol is based on the latest version of the study protocol (PROTOCOL_IDEAL2_ST_V2.3_8JAN2017). Figure 1 shows the schedule of enrolment, intervention, study visits and assessments for the study groups. Figure 2 shows the CONSORT flow chart.

**Fig. 1 Fig1:**
[figure not shown]
CONSORT *flow chart* for IDEAL-2 study

**Fig. 2 Fig2:**
[figure not shown]
Schedule of enrolment, intervention, study visits and assessments for both study groups

### Study design

IDEAL-2 is a single-centre open-label RCT, employing the following interventions (Fig. 1):A[−]Calcitriol: ACEI/ARB alone (the usual standard care for diabetic albuminuria);A[+]Calcitriol: ACEI/ARB + calcitriol.

### Interventions

In the A[+]Calcitriol group, participants will receive calcitriol 0.25 μg daily and optimised ACEI/ARB for 26 weeks. Adjustment of treatment will be based upon safety endpoints and if emerging data shows any evidence of safety concern.

In the A[−]Calcitriol group, participants will receive conventional therapy with ACEI/ARB for 26 weeks. Adjustment to the dosage of ACEI or ARB will be based upon safety endpoints and if emerging data show evidence of safety concern.

### Drug dosages

ACEI/ARB: It is expected that participants will be optimised for ACEI/ARB treatment by achieving the maximum recommended dose or, if this is not possible, the maximal tolerated dose.Calcitriol: The dose of calcitriol employed in the study is 0.25 μg (250 ng) orally per day. If the calcium level is 2.62–2.79 mmol/L in the calcitriol + ACEI/ARB group and the participant is taking calcitriol 0.25 μg daily, the individual will decrease calcitriol to 0.25 μg thrice weekly. Calcium levels will be rechecked in two weeks. If the follow-up calcium level continues to be ≥ 2.62 mmol/L, the participant will discontinue use of calcitriol for the remainder of the study. If the follow-up calcium level is < 2.62 mmol/L, the individual will continue calcitriol 0.25 μg thrice weekly. If subsequently the calcium level is > 2.62 mmol/L in the calcitriol + ACEI or ARB group and the participant is taking calcitriol 0.25 μg thrice weekly, the individual will be withdrawn from the study intervention. In the unlikely event that the repeated serum calcium level is ≥ 2.62 mmol/L in the ACEI or ARB alone group at any stage, the investigator will consider withdrawing the participant from the study and investigating this clinically.

### Recruitment and setting

Individuals will be identified, screened for eligibility and recruited from the Hamad Medical Corporation outpatient clinics. Hamad Medical Corporation is the main clinical care provider in Qatar and consists of general and specialist hospitals providing secondary and tertiary care. Participants will be identified by clinicians in the outpatient department; if they are interested in participating in the study, they will be scheduled for a screening visit. The clinician will ensure that all clinically routine blood and urine tests have been conducted to allow assessment of participant eligibility and participation. Written informed consent is taken by a trained member of the research team independent of the referring physician.

### Eligibility criteria

The eligibility criteria are designed to include individuals appropriate for the study protocol. All relevant medical and non-medical conditions will be taken into consideration by the investigator team on whether the protocol is appropriate for an individual participant.

### Inclusion criteria

Individuals must meet all of the following inclusion criteria in order to be eligible for enrolment:Age ≥ 18 years and < 80 years.Diagnosis of T2DM requiring treatment with at least one oral hypoglycaemic medication or insulin:Individuals will be considered to have established T2DM if the diagnosis of diabetes has been made and the participants were treated an oral hypoglycaemic agent or with insulin or for at least six months after diagnosis;Individuals will be considered to have newly established T2DM if the diagnosis of diabetes was diagnosed with a fasting plasma glucose ≥ 7 mmol/L (126 mg/dL) or haemoglobin A1c is > 6.5% in the past six months;Documented albuminuria, defined as a presence of albuminuria on two occasions in the last six months:i.A spot-urine ACR ≥ 30 mg/g creatinine (≥ 2.5 mg/mmol creatinine in men, ≥ 3.5 mg/mmol creatinine in women), orii.Albumin ≥ 30 mg/24 h in a 24-h urine collection, oriii.Albumin ≥ 20 μg/min in a short-time urine collection, oriv.Albumin ≥ 30 mg/L in a spot-urine sample.eGFR using the four-variable Modification of Diet in Renal Disease (MDRD) equation of ≥ 25 mL/min/1.73 m^2^.

### Exclusion criteria

Individuals will not be eligible for enrolment in the study if they fulfil any of the below criteria:If female: positive pregnancy test or planning pregnancy in the subsequent 12 months.Pregnant.Breastfeeding.Corrected serum calcium ≥ 2.62 mmol/L.Serum potassium > 5.2 mmol/L if not on ACEI or ARB; serum potassium > 6.0 mmol/L if on ACEI or ARB.25-hydroxyvitamin D (25-OH Vit D) > 80 ng/mL.PTH > 200 pg/mL.Poorly controlled hypertension defined as systolic blood pressure (SBP) ≥ 180 mmHg or diastolic blood pressure ≥ 110 mmHg.SBP ≤ 110 mmHg.History of kidney stones.History of severe chronic disease (e.g. chronic liver disease).Active malignancy.Recent diagnosis of acute renal failure within three months of screening visit.Likelihood of renal replacement therapy within one year.Any clinical and biochemical indication of primary hyperparathyroidism.History of parathyroidectomy.History of chronic diseases of malabsorption (e.g. Crohn’s disease, coeliac disease).History of cystic fibrosis.Currently taking calcitriol.Currently taking calcitonin, bisphosphonates, cinacalcet, teriparatide, glucocorticoids or other drugs that may affect calcium or bone metabolism (individuals may be taking calcium containing phosphate binder or other phosphate binder. Individuals may also be taking stable dose of oestrogen/progestin).Currently taking digitalis (cardiac glycosides).Clinical history of osteoporosis or other bone disorder and currently on calcitriol therapy.History of allergic reaction to calcitriol, paricalcitol or other 1,25-dihydroxyvitamin D analogues.History of allergic reaction to any ACEI or ARB therapy.

Participation in the study will also take into account any clinical contraindications that may preclude participation as determined by the individual’s physician or the investigator team.

Those who are clinically determined to have an active infection during any urine collection will have the urine test within one week after the resolution of the infection.

### Female participants and pregnancy

To be defined as a woman of non-child-bearing potential, one of the following criteria must be met:A physician documented history of hysterectomy (removal of the womb) and/or bilateral oophorectomy (removal of both ovaries); orAged > 55 years and post-menopausal (stopped menstrual periods) for > 24 months.

All other women are considered to be women of child-bearing potential. Appropriate precautions will be taken in the research study to guard against inadvertent exposure of fetuses to study drugs and to inform individuals of potential risk and the need for precautions. To minimise the possibility of fetal exposure in female participants of child-bearing potential, pregnancy testing will be performed at (screening visit) to detect unsuspected pregnancy before initiation of study treatment. If negative, the individuals must also not be planning a pregnancy for the duration of the study. All efforts will be made by the investigator to ascertain that the study participants will responsibly employ a reliable method of contraception or abstinence for the duration of the drug/treatment exposure. If requested, the investigator will refer the individual to a knowledgeable counsellor or physician for contraceptive advice. Should a participant become pregnant during the study or within three months of completing treatment, she must advise the investigator who will liaise with their obstetrician.

### Prohibited concomitant medications

Calcitonin, bisphosphonates, cinacalcet, teriparatide, glucocorticoids and other 1,25-dihydroxyvitamin D analogues, such as paricalcitol and doxercalciferol, are prohibited. If a participant has a medically necessary indication for the use of any of these medications, the individual will be required to withdraw from the study.

Participants will not be co-prescribed an ACEI and an ARB. Direct renin inhibitor use during the course of the study is prohibited. Individuals are permitted other antihypertensive agents that include but are not limited to: (1) thiazide diuretics; (2) calcium channel blockers; and (3) beta blockers. Local and international clinical guidelines for management of blood pressure in patients with DKD will be followed.

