### Visits

Individuals will either be required to return to the study site for the outpatient visits and/or have follow-up phone calls for safety and other evaluations post randomisation at weeks 2, 4, 8, 12, 16, 20, 24 and 26.

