### Participant withdrawal and safety measures

The investigators will determine whether a participant will withdraw due to an adverse event. At any point in time, the individuals can withdraw from the study. Safety measures include blood pressure and serum creatinine, potassium and corrected calcium. The key withdrawal and safety criteria include:SBP ≤ 110 mmHg.Serum creatinine increase > 25% of the baseline level (study entry).Confirmed serum potassium > 6.0 mmol/L.Corrected serum calcium ≥ 2.80 mmol/L on one test or repeated corrected serum calcium is 2.62–2.79 mmol/L, despite dose adjustmentWomen who become pregnant during the study will be withdrawn with review to ensure safety for the mother and fetus.

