### Sample size calculations

A sample size of 320 individuals will be enrolled in the study. Based on the VITAL study, we estimate a treatment effect for albuminuria of d = 0.25 sd and an intraclass correlation coefficient of 75% for our current study. To achieve a power of 80% to detect a statistically significant treatment effect for a two-tailed test with α = 0.05, we calculate a minimum of 256 participants. To cater for a potential dropout of 20%, we will enrol a total of 320 individuals.

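### Two rules take participants out of the study, where stopping or changing treatment would do, and so can discard ACR values that the intention-to-treat analysis needs (minor)

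*Protocol article*

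**What the plan says.** **Prohibited drugs.** Prohibited concomitant medications lists calcitonin, bisphosphonates, cinacalcet, teriparatide, glucocorticoids and other active vitamin D analogues. If one becomes medically necessary, "the individual will be required to withdraw from the study". The rule is mandatory, covers both arms and has no time limit. By contrast, the withdrawal list under Run-in period is expressly confined to the time before randomisation.

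**Raised calcium, calcitriol arm.** Drug dosages first reduces the dose. If calcium is still raised at the two-week recheck, "the participant will discontinue use of calcitriol for the remainder of the study". If it rises later on the thrice-weekly dose, "the individual will be withdrawn from the study intervention".

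**Raised calcium, control arm.** The same section calls a repeated value of 2.62 mmol/L or more unlikely. If it happens, "the investigator will consider withdrawing the participant from the study and investigating this clinically".

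**General criteria.** Participant withdrawal and safety measures lists calcium of 2.80 mmol/L or more on one test, or that "repeated corrected serum calcium is 2.62–2.79 mmol/L" despite dose adjustment. It does not say whether the participant leaves treatment or the study.

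**Analysis.** Statistical analysis plans a mixed model on ACR at every post-randomisation time point under intention-to-treat. Sensitivity analyses are multiple imputation by chained equations (20 datasets) and a per-protocol analysis. Contacts are planned "post randomisation at weeks 2, 4, 8, 12, 16, 20, 24 and 26".

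**The concern.** Stopping study treatment and leaving the study are separate decisions, and the article has words for both. Drug dosages speaks of withdrawal from the intervention, so withdrawal from the study reads naturally as ending participation. On that reading, a randomised participant given a course of glucocorticoids at week 10 contributes no later ACR, although the intention-to-treat comparison needs that value and the visit timetable still runs to week 26.

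No analysis plan can restore values that were never collected. Nor is study exit needed to keep prohibited drugs out of an on-protocol estimate, because the planned per-protocol analysis can leave those participants out.

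Two things are at stake. One is what the primary estimate means: the effect of assignment, or the effect in people who never needed these drugs. The other is a modest draw on the dropout allowance. The trial is open-label and was underway when the article was written, so such losses could be avoided only prospectively.

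**Working it through.** **Inputs from the article.** Sample size calculations: effect 0.25 SD, intraclass correlation 0.75, two-sided 5% level, 80% power, at least 256 participants, and "To cater for a potential dropout of 20%, we will enrol a total of 320 individuals". Randomisation is 1:1, so 160 per arm.

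**The plan's own figures.** With change-score variance, the SD is √(2 × (1 − 0.75)) = 0.707. Per arm, n = 2 × (1.960 + 0.842)² × 0.707² / 0.25² = 125.6, so 126, or 252 in total. That is close to the stated 256. Then 256 / 0.80 = 320, as stated. The allowance is 320 − 256 = 64 people. The sample-size arithmetic is not at fault.

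**Slack in the allowance.** Starting from 320 on the change-score basis, power by total loss is:

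| Loss | Power |
|---|---|
| 0% | 88.5% |
| 20% | 80.7% |
| 22% | 79.8% |
| 25% | 78.2% |

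With baseline-adjusted (ANCOVA) variance, 1 − 0.75², which is closer to the planned model, power is 85.6% at 20% loss and still 80.7% at 30%.

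**Prohibited-drug rule (illustration; all rates assumed).** Let w be the share leaving in each arm and r the share of the 0.25 SD benefit that calcitriol leavers would keep.

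- Effect of assignment = 0.25 × (1 − w × (1 − r)).
- w = 0.01, r = 0: 0.2475.
- w = 0.05, r = 0.5: 0.24375.
- w = 0.05, r = 0: 0.2375.
- r = 1, any w: 0.25.

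If exits are random and equal by arm, the estimate without post-exit values is about 0.25. The gap is therefore 0 to 0.0125 SD, and the largest ratio is 0.25 / 0.2375 = 1.053. A simulation with baseline adjustment agrees to within 0.001 SD in the w = 0.05, r = 0 case: about 0.25 with exits lost and about 0.238 with exits followed.

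In people, 320 × 0.01 = 3.2 and 320 × 0.05 = 16, which is 5% to 25% of the 64 places.

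**Control calcium rule (illustration; rates assumed).** Suppose 0.5–2% of controls leave (160 × 0.005 = 0.8; 160 × 0.02 = 3.2 people) and their unseen log ACR departs from the model by 0.25–0.5 SD in either direction. The group difference then shifts by 0.005 × 0.25 = 0.00125 SD to 0.02 × 0.5 = 0.010 SD, which is 0.5% to 4% of 0.25.

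**Against the trial's precision.** The standard error implied by 80% power is 0.25 / (1.960 + 0.842) = 0.0892 SD. The largest shift above is 0.0125 / 0.0892 = 0.14 standard errors.

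**The case against.** **Arm asymmetry.** From Drug dosages alone, a reader might infer that raised calcium sends controls out of the study while calcitriol participants only stop the drug, so that outcomes go missing differently by arm. The article does not establish this. The general withdrawal criteria do not say what the participant withdraws from, and the reference to dose adjustment points to the calcitriol arm, the only one with a calcium-driven dose reduction. Calcitriol participants may therefore leave the study too. The control rule is also discretionary, needs a repeated value and concerns an event called unlikely. Controls have no calcitriol to stop, and unexplained raised calcium does need a work-up. This part of the objection stands.

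**Condensed article.** The full protocol may provide for follow-up after withdrawal, and the article's withdrawal terms vary. This limits certainty, but the prohibited-drug rule is a stated instruction and not a missing detail.

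**Mitigation already planned.** The mixed model keeps ACR recorded before exit, imputation is planned as a sensitivity analysis, and the 20% allowance covers dropout in general. These soften the loss but do not replace observed values.

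**Small and not clearly bias.** The exclusion criteria already bar anyone "Currently taking calcitonin, bisphosphonates, cinacalcet, teriparatide, glucocorticoids or other drugs that may affect calcium or bone metabolism", so new need within 26 weeks should be uncommon. It is also tempting to call the 0–5% gap bias against calcitriol or in its favour. With equal random exits it is the distance between two estimands, and the article gives no basis for a direction. This stands too.

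**Conclusion.** The point holds as a minor one. The prohibited-drug rule, and at the investigator's discretion the control calcium rule, can remove post-randomisation ACR values that the intention-to-treat analysis is meant to use. The first applies equally to both arms and the second should be rare. Under assumed exit rates of 1–5% per arm for prohibited drugs and 0.5–2% of controls for calcium, no shift exceeds 0.0125 SD against the planned 0.25 SD. The larger figures need 5% of each arm to start a listed drug and lose all benefit. None of these rates comes from the article.

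What remains unsettled is whether the general calcium criteria end treatment or participation. Either answer supports clarification. If they end treatment, only the control rule in Drug dosages still speaks of leaving the study. If they end participation, they conflict with Drug dosages.

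**What to change.** 1. In Prohibited concomitant medications and in the control-arm calcium rule under Drug dosages, replace withdrawal from the study with: study treatment is stopped or changed as clinically needed; the participant is followed to week 26 unless consent is withdrawn.
2. In Participant withdrawal and safety measures, state that the calcium criteria stop calcitriol only, consistent with Drug dosages. The other criteria in that list are outside this point.
3. Keep every safety threshold and the clinical work-up.
4. Include the later ACR values in the intention-to-treat model. Leave out prohibited-drug users only in the planned per-protocol analysis.

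The cost is a wording change in three sections and a few extra measurements on the existing timetable. Some scheduled contacts may be telephone calls, so the values to secure are those at urine-sampling visits, above all week 26. The statistical cost is slight dilution from off-treatment values, at most 0.0125 SD in the illustration.
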